## Abstract

**Background:**

Scoliosis is present in 3-5% of the children in the adolescent age group, with a higher incidence in females. Treatment of adolescent idiopathic scoliosis is mainly dependent on the progression of the scoliotic curve. There is a close relationship between curve progression and rapid (spinal) growth of the patient during puberty. However, until present time no conclusive method was found for predicting the timing and magnitude of the pubertal growth spurt in total body height, or the curve progression of the idiopathic scoliosis.

The goal of this study is to determine the predictive value of several maturity indicators that reflect growth or remaining growth potential, in order to predict timing of the peak growth velocity of total body height in the individual patient with adolescent idiopathic scoliosis. Furthermore, different parameters are evaluated for their correlation with curve progression in the individual scoliosis patient.

**Methods/design:**

This prospective, longitudinal cohort study will be incorporated in the usual care of patients with adolescent idiopathic scoliosis. All new patients between 8 and 17 years with adolescent idiopathic scoliosis (Cobb angle >10 degrees) visiting the outpatient clinic of the University Medical Center Groningen are included in this study. Follow up will take place every 6 months. The present study will use a new ultra-low dose X-ray system which can make total body X-rays. Several maturity indicators are evaluated like different body length dimensions, secondary sexual characteristics, skeletal age in hand and wrist, skeletal age in the elbow, the Risser sign, the status of the triradiate cartilage, and EMG ratios of the paraspinal muscle activity.

Correlations of all dimensions will be calculated in relationship to the timing of the pubertal growth spurt, and to the progression of the scoliotic curve. An algorithm will be made for the optimal treatment strategy in the individual patient with adolescent idiopathic scoliosis.

**Discussion:**

This study will determine the value of many maturity indicators and will be useful as well for other clinicians treating children with disorders of growth. Since not all clinicians have access to the presented new 3D X-ray system or have the time to make EMG's, for example, all indicators will be correlated to the timing of the peak growth velocity of total body height and curve progression in idiopathic scoliosis. Therefore each clinician can chose which indicators can be used best in their practice.

**Trial registration number:**

NTR2048

## Background

Scoliosis is present in 3-5% of the children in the adolescent age group, with a higher incidence in females. The cause of scoliosis in this age group is unknown in the majority of cases (80-85%), and it is therefore called adolescent idiopathic scoliosis (AIS).

Successful treatment of AIS remains a complex challenge for the orthopaedic surgeon. Generally, treatment is conservative (observational or brace therapy) until curves progress to more that 45-50 degrees Cobb angle. Scoliotic curves larger than 50 degrees need surgical treatment. Accurate timing of treatment, whether this is conservative or surgical, plays an essential role in the prognosis of the condition, and in prevention of severe complications like the crankshaft phenomenon[1]. The timing of treatment is mainly dependent on the progression of the scoliotic curve. For optimal treatment, it is important to understand if and when the curve will progress. However, exact prediction of curve progression in patients with adolescent idiopathic scoliosis is still impossible since the prognosis of the deformity is different in each individual.

A known relationship exists between growth of the patient and development of the spinal deformity. It is shown that a rapid increase in (spinal) height at the time of the pubertal growth spurt causes an increase in spinal curvature[2-7]. So, progression of AIS is closely related to rapid growth, and it is therefore likely that understanding longitudinal growth of the patient during puberty is the most important dimension in (treatment of) adolescent idiopathic scoliosis. In order to predict curve progression, it is of great interest to predict the timing and magnitude of the peak growth velocity in the individual patient with idiopathic scoliosis.

The peak growth spurt is known to take place between 10 and 14 years in 95% of the girls, and between 12 and 16 years in 95% of the boys[8,9]. This range holds for a large population, but is too wide to make accurate predictions in the individual patient. However, several other maturity indicators are related to the pubertal growth spurt. Maturity is multidimensional and has various components, including chronological age, skeletal age in different areas, the Risser sign, status of the triradiate cartilage, Tanner stage of sexual maturation, age at thelarche and menarche, and several length dimensions like sitting height, subischial leg length, and foot length or shoe size. These indicators of maturity are all signs that reflect growth or remaining growth of the patient and can be useful in predicting timing of the pubertal growth spurt or peak growth velocity of total body height in the individual patient.

Researchers have tried to find different ways to predict curve progression in AIS as well, besides relating progression to the peak growth velocity of height. A promising method was shown by Cheung et al[3,10], who found a relationship between curve progression and altered electromyography ratios of the convex and concave sides of the curve. Enhanced EMG ratios were observed at three levels of the scoliotic curve (lower end vertebra, apex, and upper end vertebra) at the start of progressive periods. At the start of a non-progressive period, such an enhanced EMG ratio was only observed at the level of the apex vertebra[3].

Only few studies have investigated maturity indicators in patients with idiopathic scoliosis[11-14]. Moreover, studies have compared only some of these indicators, and only either in relationship to the peak growth velocity of total body height, or to curve progression, not to both in one study. Results of different studies are contradictory and inconsistent, so therefore a good algorithm for determining treatment options in AIS is still lacking.

The goal of this study is to determine the predictive value of several maturity indicators that reflect growth or remaining growth potential, in order to predict timing of the peak growth velocity of total body height in the individual patient with adolescent idiopathic scoliosis. Furthermore, different parameters are evaluated for their correlation with curve progression in the individual scoliosis patient. An algorithm is made for determining the optimum treatment strategy in the individual patient with adolescent idiopathic scoliosis.

A description of the maturity indicators is presented below.

### Body length dimensions

It is known that different body length dimensions each have their own typical growth pattern influenced by age- and gender-related factors. Research has been done by Welon and Bielicki[15], Cameron et al[16], Dimeglio[17], and Rao et al[18] to the sequences of peak growth velocities of different length measurements of children from 1-18 years. They all confirm the distal-to-proximal growth maturity gradient as described by Tanner[19]. Body parts that are more distal will have their pubertal growth spurt earlier in adolescence. Furthermore, it is known that the sequence of growth spurts of different length measurements is similar in individual children, regardless of being an "early" or "late" maturer[4,20]. Therefore different body length growth velocities can be useful in predicting peak growth velocity of total height.

In order to calculate growth velocities, access is needed to longitudinal growth data of the patient. It is useful when a patient already has some measurements known at the first visit to the outpatient clinic. Usually that happens very rarely. However, as foot length is said to be the body dimension with the earliest pubertal growth spurt[17,18,21-23], patients were asked if they could recall the course of their shoe size. In a pilot study, it was shown that patients and their parents can recall to a high extend when they bought new shoes and what their shoe size was for approximately the last 2 years. This could therefore be a better measurement than foot length. However, this study should investigate the possibility of a recall bias in a larger dataset, as well as the reliability of the provided information.

### Skeletal age dimensions

Any skeletal region with consistent physeal markers is amenable to be a determination of skeletal age. The most commonly used markers of skeletal age in patients with idiopathic scoliosis are the hand, wrist and the ossification of the iliac apophysis (Risser sign).

Unfortunately, there is a fairly wide range of skeletal age compared with pubertal stages and pubertal growth, although the variation is less than with chronological age.

Determination of skeletal age by hand and wrist X rays is usually done by the method of Greulich and Pyle or Tanner and Whitehouse. The latter is more reliable and reproducible but also fairly complex and time consuming. The Tanner Whitehouse classification can predict well if the patient is pre- or post pubertal growth spurt. The Greulich and Pyle method of assessing skeletal age is easier to use but less precise, and the atlas was compiled from radiographs made in the 1930s [24].

The Risser sign (ossification of the iliac apophysis) continues to be an accepted prognostic sign in the evaluation of growth of patients with idiopathic scoliosis. There is, however, considerable and growing controversy[12-14,25-27]. Disadvantage of using the Risser sign is the wide distribution and the fact that it typically appears after de peak growth velocity of height. Risser stage 1 occurs after the growth spurt in 85% of patients, so its predictive value is very low.

Sanders et al[12] found the status of the triradiate cartilage to be more predictive for the timing of the peak growth velocity of total body height, though it is only predictive whether the patient is before or after the pubertal growth spurt. Once the patient had closed triradiate cartilages, he or she is very likely past the pubertal growth spurt. However, the predictive value of open triradiate cartilages is less clear.

A different method for describing skeletal age is the Sauvegrain method, in which skeletal age is determined using a scoring system for four anatomical landmarks of the elbow. At the onset of puberty, the elbow is still largely cartilaginous. Two years later, fusion of the elbow growth centers is complete. This period is critical since it is marked by the pubertal growth spurt. This method was found to be more accurate and detailed than the Gruelich and Pyle atlas[28]. Furthermore, it is easy to use, and it allows the evaluation of skeletal age in six-month intervals, in contrast to one-year intervals in the most commonly used methods of Gruelich and Pyle, and Tanner and Whitehouse.

### Secondary sexual characteristics

Another hallmark of maturation is de development of secondary sexual characteristics, often classified by Tanner. Thelarche, the first stage of secondary breast development, marks the beginning of puberty and usually takes place 1 year before the peak growth velocity of height[4,11,29,30]. Girls typically reach peak growth velocity of height between stage 2 and 3 of breast development and pubic hair development. The pubertal or Tanner stages are good measurements of maturity. However, most orthopaedic surgeons are uncomfortable in evaluating secondary sexual characteristics with their patients, and self assessment of patients is said to be unreliable. Timing of menarche, the first menstrual period, can be used in girls, but most often takes place 1 year after PHV and is therefore always retrospective. It is assumed that the timing of menarche of the child is closely related to the timing of menarche of the mother. When the mother can recall the timing of her menarche, some predictions can be made for the timing of menarche of the child, and therefore for the timing of the pubertal growth spurt. However, it is still unknown how accurate this relationship is.

## Methods/design

### Study design

A prospective, longitudinal cohort study will be conducted at the outpatient clinic of the department of orthopaedic surgery of the University Medical Center Groningen (UMCG).

The collection of the data will be part of the usual follow up for patients with adolescent idiopathic scoliosis. Approval has been requested from the Medical Ethics Committee for this study, but ethical approval was waived by the Committee, since the collection of the data is part of the usual care in our outpatient clinic.

Informed consent is obtained from each patient and his or her parents before data collection.

### Identification and recruitment of study participants

Patients between 8 and 17 years old, visiting the outpatient clinic of the UMCG with adolescent idiopathic scoliosis will be participating in this study. The Cobb angle should be >10 degrees, measured by an experienced observer on an AP X-ray of the total spine.

Patients should not have had previous spinal surgery; there should be no evidence of neuromuscular disease or skeletal dysplasia, and no evident abnormalities of maturation or height. Furthermore, patients with mental incapacitation are excluded since this can influence the reliability of the measurements in the way that these patients most often can not stand still during the height measurements and EMG measurements. Patients are excluded as well when they are participating in a different study simultaneously.

The assessment to include or exclude a patient will be determined by the orthopaedic surgeon. All patients who meet the inclusion criteria will be asked to participate in this study and give their informed consent.

### Study protocol

The study protocol will be incorporated in the usual care of patients visiting the outpatient clinic for follow up of adolescent idiopathic scoliosis. Follow up will take place every six months. Patients will be followed until 18 years of age or until growth of the spine has stopped and skeletal maturity has been reached. Furthermore, patients will be lost to follow up when they receive surgical treatment.

A description of the (follow up) consult is presented below.

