### Outcome measurements

Longitudinal data will be acquired for:

• Scoliotic curve progression (in degrees Cobb angle)

• Height, and growth velocity of height

• Sitting height, and growth velocity of sitting height

• Leg length, and growth velocity of leg length

• Foot length, shoe size, and growth velocity of foot length and shoe size

• Weight, and growth velocity of weight

• Spinal length, and growth velocity of spinal length

• Tanner stage of secondary sexual characteristics

• Riser sign and status of the triradiate cartilage

• Skeletal age in hand, wrist, and elbow

• EMG ratios of the paraspinal muscles

Finally, an algorithm will be developed for predicting peak growth velocity of height and curve progression in individual patients with adolescent idiopathic scoliosis (see Figure 4). 

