### Sample size and statistical analysis

The maximum sample size of this study is not determined on beforehand, as the study is aimed to proceed for the coming years.

We aim to perform a first preliminary analysis of the longitudinal data when patients have a follow up of at least 2 years. As the expected number of new patients is 60 each year, it will take 2.5 years for 30 patients to reach a follow up of at least 2 years. Taking a loss to follow up into account due to surgical treatment, we expect to be able to analyse the complete data of at least 25 patients. The statistical power will increase with a longer follow up and more patients. The number of 25 patients was checked whether it was large enough to obtain a good prediction model according to the criteria of Knofczynski and Mundfrom [33]. With a significant large influence of 4-5 predictor variables (as is expected in this study) and a squared multiple correlation coefficient between 0.5 and 0.7 between 25 and 65 patients should be included. Therefore the first preliminary analysis will be performed using data of 25 patients.

Individual data charts are made, and results of each parameter are plotted against the growth velocity of total body height and the curve progression.

All statistical calculations are made using SPSS (SPSS Inc, Chicago USA). Pearson correlation coefficients are computed for each individual possible related parameter against the peak growth velocity and the curve progression (Figure 5). A correlation above 0.70 is believed to be clinically relevant. To be able to interpret this value in a reliable way, we will report the confidence intervals as well.

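### Surgery is an outcome-related exit, so a complete-data analysis of curve progression is selected on curve severity and its correlations and coefficients are distorted

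*Protocol article*

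**What the plan says.** Four parts of the protocol article bear on this.

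- **Exit rule (Study protocol).** Visits are six-monthly until age 18 or skeletal maturity, and "patients will be lost to follow up when they receive surgical treatment".
- **What leads to surgery (Background).** As a description of general practice, "treatment is conservative (observational or brace therapy) until curves progress to more that 45-50 degrees Cobb angle", and "Scoliotic curves larger than 50 degrees need surgical treatment".
- **Outcome (Outcome measurements).** The first item listed is "Scoliotic curve progression (in degrees Cobb angle"), which is a change in the same quantity that leads to surgery.
- **Analysis set (Sample size and statistical analysis).** The accrual statement is "As the expected number of new patients is 60 each year, it will take 2.5 years for 30 patients to reach a follow up"; the period meant is 2 years. The shortfall is then put down to operations, and the article says: "we expect to be able to analyse the complete data of at least 25 patients".

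Pearson correlations, with 0.70 as the level of clinical relevance, and multiple linear regression are then run against curve progression. The missing-data paragraph deals with a wholly missed visit and with a single missing parameter. It does not mention surgery.

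**The concern.** Loss to follow-up is harmless to a correlation only if it is unrelated to the outcome, given what is analysed. Here it is related. A patient leaves because the curve has become large, and the planned set is what remains afterwards. Curve progression is one of the two targets of the study and feeds the treatment algorithm, so a distorted equation would be least reliable for patients heading towards surgery, for whom the Background calls timing essential.

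The article expects power to grow with more patients and longer follow-up. That helps precision only. If the same rule is carried into later analyses, the selection stays the same size however large the cohort becomes.

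**Working it through.** **1. The plan's own figures.** With 60 patients a year and 2.5 − 2.0 = 0.5 years of early enrolment, 60 × 0.5 = 30 patients can reach 2 years. Going from 30 to 25 is a loss of 5/30 = 16.7%. Both figures reproduce. The loss fraction is the only selection input that the article gives; all SDs below and the normal distributions are assumptions.

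**2. Worst case: the top sixth on progression itself is lost.** For a normal outcome cut at c = z(0.833) = 0.967:

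- λ = φ(c)/Φ(c) = 0.300
- variance ratio u² = 1 − cλ − λ² = 1 − 0.290 − 0.090 = 0.620, so u = 0.787
- r′ = r·u / √(1 − r² + r²u²)
- for r = 0.70: 0.70 × 0.787 / √(0.51 + 0.49 × 0.620) = 0.551/0.902 = 0.61

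By the same formula 0.50 becomes 0.41 and 0.30 becomes 0.24. The article's assumed R² of 0.5 becomes 0.38, and 0.7 becomes 0.59. If 5%, 10% or 25% were lost instead, r = 0.70 would become 0.66, 0.64 or 0.58.

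**3. Selection as the Background describes it: on the level reached.** Final Cobb = baseline + progression, and the highest sixth on final Cobb is removed. I simulated 1,000,000 patients per scenario. The SD pairs (baseline/progression, degrees) were 10/8, 8/8, 10/5 and 5/10, each with a baseline–progression correlation of −0.3, 0 or +0.3.

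| Link with progression | True r | r in the retained five-sixths |
|---|---|---|
| Indicator that predicts progression | 0.70 | 0.63 to 0.70 |
| Baseline curve | 0 | −0.19 to −0.23 |
| Baseline curve | −0.30 | −0.44 to −0.50 |
| Baseline curve | +0.30 | +0.07 to +0.10 |
| Marker correlated 0.7 with baseline curve (baseline itself unrelated) | 0 | −0.12 to −0.16 |

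With SDs of 10/8 and no baseline–progression correlation, the 0.70 becomes 0.67. Mean progression is understated by 0.06 to 0.28 SD across the scenarios.

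**4. Regression, SDs 10/8, standardised units.** The coefficient of the true predictor falls from 0.70 to 0.62, and baseline curve, with a true coefficient of 0, receives −0.14.

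**5. Sampling error for comparison.** By Fisher's z, the 95% interval for r = 0.70 is tanh(0.867 ± 1.96/√(n − 3)). This gives 0.42 to 0.86 at n = 25 and 0.45 to 0.85 at n = 30. Keeping the five patients therefore gains little precision; the gain is in removing the selection.

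**The case against.** The strongest reply has four parts.

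- **The exit sentence only ends follow-up.** This is correct, and ending it there is reasonable, since Cobb change after an operation is not natural progression. A reader might infer that operated patients' earlier visits are discarded throughout the study. The article does not say so. The exclusion rests on the sample-size section ("Taking a loss to follow up into account due to surgical treatment, we expect to be able to analyse the complete data") and is stated only for the first, preliminary analysis; later use of pre-operative visits is left open.
- **Links need not all shrink.** A reader might infer that every correlation with progression is biased toward zero because the removed patients are the fastest progressors. The documents do not support that. Surgery depends on the level reached, and entry requires a Cobb angle above 10 degrees with no upper limit, so a patient who enters with a large curve can leave after little change. Steps 3 and 4 show some links moving away from zero.
- **The size is modest.** The fall to 0.61, and the matching fall in slope from 0.70 to 0.53 (0.70 × 0.620/0.814), need the lost patients to be exactly the top progressors. Under level-based selection the attenuation is a few hundredths, small against the interval at n = 25, and the article will report intervals. This stands for a single sample, but the bias is systematic and does not average out. As the article expects at least 25 complete patients, 5/30 is also the upper end of the planned loss.
- **Detail is commonly left to a fuller document.** That does not answer the point. The article itself states the complete-data set and attributes the shortfall to surgery.

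It also stands that the main stated goal is the timing of peak growth velocity; no effect on that goal is shown here.

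**Conclusion.** The point holds for curve progression. Following the article as written, the first analysis is run on patients selected by curve severity. A predictor with a true correlation of 0.70 would be seen at about 0.63 to 0.70, and at 0.61 in the worst case. Because 0.70 is the relevance bar, even this moderate loss can put a relevant indicator below it. Links with baseline curve size and its correlates can be created, strengthened in the negative direction or nearly erased, so the error cannot be treated as merely conservative.

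The sizes rest on normal distributions, a loss of one sixth, SDs of 5 to 10 degrees and a sharp cut on final Cobb angle. Where other considerations also decide on surgery, the selection is less sharp and the distortion smaller. The direction for any one indicator depends on how it relates to baseline curve and to progression.

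**What to change.** Amend Study protocol and Sample size and statistical analysis to say:

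- Surgery ends follow-up, but operated patients stay in the curve-progression analysis with all visits up to the last one before surgery. Complete 2-year data are not required of them.
- Progression is analysed on a scale that allows unequal follow-up, for example Cobb change per year, or a longitudinal model using all pre-operative visits. The second is preferable where exit depends on Cobb angles already recorded, because those values are then in the model.
- Baseline Cobb angle and maturity indicators are reported for operated versus non-operated patients.
- The complete-case result is given as a sensitivity analysis.

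A combined event of progression or surgery is optional at most: about five operations are expected, and the article defines no progression threshold.

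The cost is a change of wording and of analysis, with no change to care. The six-monthly visits should usually supply pre-operative data. However, no dedicated pre-operative X-ray is documented, and a patient operated on before the first follow-up visit contributes no change. Follow-up length will differ between patients. Annualised change over a short interval is noisier and assumes roughly constant progression, which sits uneasily with the article's own link between progression and the growth spurt.
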